| Secondary Objective(s)                             | The secondary objective is to compare adverse outcomes, treatment-related pain, length of stay, disability days, costs and burden of care and quality of life measures, and disease-related stigma and attitudes between those that receive laser hair depilation plus mechanical/chemical hair depilation with those that receive only mechanical/chemical hair depilation.                                                                                                                                                                                                                                             |
| Research Intervention(s)/ Investigational Agent(s) | Laser hair depilation: It was determined by the Director of the Drug and Device Development Services and the Institutional Review Board (IRB) at NCH that an investigational device exemption is not necessary because we are using an approved device for investigational purposes with non-significant risk. Laser use in this study poses minimal risk to the patient and these minimal risks are similar to the risks associated with hair removal in other regions of the body for which these devices are already FDA approved.                                                                                    |
| IND/IDE #                                          | N/A                                                                                                                                                                                                                                                                                                                                                                                                                                                                                                                                                                                                                      |

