## 2.0 Objectives

2.1 The present study is a follow-up study to IRB16-00104. The objective of this study is to perform a randomized controlled trial of laser hair depilation + chemical/mechanical depilation versus

chemical/mechanical depilation only to examine outcomes related to recurrence of pilonidal disease. Recurrence is defined as a new development of pilonidal abscess, folliculitis, or draining sinus after treatment which would require antibiotic treatment, additional surgical incision and drainage or excision.

The secondary objective is to compare adverse outcomes, treatment-related pain, length of stay, disability days, costs and burden of care and quality of life measures, and disease-related stigma and attitudes between those that receive laser hair depilation plus mechanical/chemical hair depilation with those that receive only mechanical/chemical hair depilation.

2.2 We recently completed a single arm pilot study at NCH which demonstrated the safety and tolerance of laser depilation in adolescents and young adults (IRB16-00104). We enrolled 13 patients and treated them with either an 810 nm wavelength laser (for Fitzpatrick skin types I-IV) or Nd:YAG laser (for Fitzpatrick skin types V-VI) monthly for 5 treatments. Twelve patients completed at least 4 laser depilation treatment sessions with 100% tolerability and no second degree burns. No patients were unable to complete a treatment session due to discomfort. All 13 patients remain recurrence-free at 13 months after the initiation of treatment with significantly diminished hair growth noted in all patients after 3 treatments. These results confirm that laser hair depilation is both safe and well tolerated in adolescents and young adults with pilonidal disease and may represent a promising therapy to decrease disease recurrence.

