disulfide bonds in keratin and weakens the hair so that it is easily scraped off where it emerges from the hair follicle. The hair follicle does remain with hair regrowth noted in 2 to 5 days and there can be some local skin irritation on the site of application. Some studies have explored the utility of certain skin glues to close the chronic tracts associated with chronic pilonidal disease. One such study utilized Fibrin glue been injected into these chronic tracts after simple curettage with some positive effect. Overall, studies of sclerosing agents and glue have yielded variable results with limited long term efficacy.

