| Disease-related stigma                           | X             |         |         | X       |         |         | X       |          |          |          |
| Disease-related attitudes                        | X             |         | X       |         |         | X       |         | X        |          |          |

4.2 Data will be monitored by research team members once a week to ensure that all data (clinical data and questionnaires) collected are correctly completed. The proportion of patients that have a study related SAE (second degree burn or pain score >8) will be calculated after every group of 10 patients have completed their course of treatment. If the lower limit of the 95% confidence interval for this proportion exceeds 10%, the trial will be stopped. A Data Safety and Monitoring Committee (DSMC) has been formed and will meet every 6 months throughout the period during which patients are being recruited and through their first year of follow-up. The DSMC will review data provided by the primary study statistician and other study staff involved in data management and analysis. [name] (pediatric surgeon, Seattle Children's Hospital) will act as the chairman of the DSMC, and will serve alongside [name] (pediatric surgeon, Vanderbilt) and [name] (Statistician/Researcher, Nationwide Children's Hospital). The study principal investigator will be made aware of all adverse events as they occur and a quarterly review of all adverse events (AEs) that occur in the trial will be performed by the study team. All unexpected non-serious AEs and SAEs relating to participation in the study will be reported verbally and in writing to the study PI and NCH IRB. The verbal report will occur within 48 hours of the occurrence. The written report of a SAE (e.g., death or life-threatening adverse event) will be reported within 7 days.

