**Table 3. Number of patients with an SAE needed to stop the study early:**

| Number of laser treatment patients | If this many or more with an SAE, the study will be stopped | 95% LCL if this number with an SAE | 95% UCL if this number with an SAE |
|------------------------------------|-------------------------------------------------------------|------------------------------------|------------------------------------|
| 10                                 | 3                                                           | 0.103                              | 0.608                              |
| 20                                 | 5                                                           | 0.108                              | 0.473                              |
| 30                                 | 7                                                           | 0.115                              | 0.412                              |
| 40                                 | 8                                                           | 0.102                              | 0.350                              |
| 50                                 | 10                                                          | 0.111                              | 0.332                              |
| 60                                 | 11                                                          | 0.104                              | 0.301                              |
| 70                                 | 13                                                          | 0.111                              | 0.294                              |

An interim analysis is planned when a quarter of the planned total patients (26 patients in each group) have completed their 1 year follow-up and a final analysis will be performed when all patients have completed 1 year of follow up. These two analyses have been unequally spaced in order to ensure that the interim analysis is performed before study enrollment is complete. The interim analyses will be interested in assessing futility of the primary endpoint; the trial will be monitored based on the primary outcome of the proportion of patients with recurrent pilonidal disease and will employ the error spending function approach described by Lan and Demets and the error spending function described by O'Brien and Fleming.

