### 6.3 Describe:

- Attending surgeons and clinical staff in the surgical clinic will be managing the clinical care of the participants. Vital signs, physical exam and pain scores will be assessed per nursing protocol and surgical service standards. An attending surgeon will assess each patient before and after each treatment. A research team call schedule will be maintained with a member of the study team available by pager 24 hours per day. Any suspected adverse event identified by this person will be discussed with the study PI.
- The laser treatment group will consist of an 810 nm (for Fitzpatrick skin types I-IV) or Nd:YAG (for Fitzpatrick skin types V-VI) 28 joule application at auto pulse duration for 400 ms. A cooling platform and application of 7% lidocaine/ 7% tetracaine cream, applied 45 minutes prior to treatment, will minimize any discomfort associated with the heat of the laser treatments.

The two lasers that will be used in this study (810 nm or Nd:YAG) are both FDA approved for hair removal in all areas of the human body including the back and perineum.

- All baseline and outcome data will be stored electronically in a Research Electronic Data Capture (REDCap) database, which can be accessed only by the appropriate research staff. All

data will be collected in a central REDCap database housed at Nationwide Children's Hospital. To minimize variation and improve the consistency of the interpretation of clinical information, we will utilize standardized data collection forms with established definitions for all variables. See attachment for all surveys/data collected. Although many of our patients return to our institution for subsequent care, some patients may receive care outside of our institution. For patients that receive care outside of our institution, we will capture the events by patient/family report during the follow-up interviews or through medical record review. We will ask for consent from the patient/family and attempt to get the medical records for these encounters to allow us to collect as detailed information about these events as possible.

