## **17.0 Data Management\* and Confidentiality**

17.1 The means/medians and standard deviations/interquartile ranges of the prognostic variables will be evaluated in the total study sample and will be compared between groups using t-tests or Mann Whitney U tests for continuous variables and chi-squared tests for categorical variables. For the primary outcome of recurrence within one year, we will calculate this proportion and its 95% confidence interval, based on the exact binomial distribution, in both treatment groups and compare this proportion between groups using a Chi-squared test.

Other outcomes will be compared using chi square tests, if categorical, and t-tests or Mann Whitney U tests as appropriate if continuous. In analyses that include outcome data collected after patients in the control group were offered laser treatment, both intention-to-treat and per-protocol analyses (with control group patients analyzed according to the treatment they received and according to the time from the start of their laser treatment) will be performed. SAS Enterprise Guide (Cary, NC) will be used for the statistical analyses.

The sample size needed to assess the primary outcome of the proportion of patients with recurrent pilonidal disease at 1-year is based on: 1) previous published studies and institutional data on the recurrence rates of pilonidal disease and 2) the efficacy of laser hair depilation treatment to reduce pilonidal disease recurrence in previous studies and our institutional pilot study. In this RCT, the recurrence rate within 1 year is expected to be 12% in the control group and a maximum 2% in the laser group. Based on these estimated recurrence rates, under a group sequential design with one interim and one final analysis, an overall type I error rate (two- sided) of 5 % and power of 80%, the sample size required for this trial is 122 patients in each treatment group. Assuming a 10% drop out rate over the course of the 1 year follow-up, we will plan to enroll 136 patients in each group (total; n=272 patients). The total of patients increased to 302 due to reasons related to COVID described above.

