**Sample Study Data Collection Questionnaire: Pilonidal Management**

**(Child):**

The items below will be modified to reflect the appropriate time point in the study

For baseline: wording will be modified to say, in the last month...

For the treatment phase: wording will be modified to say, since you last treatment...

For the follow-up time points: wording will be modified to say, since your last follow-up...

1. In the last month, how many days did you experience pain due to your pilonidal disease?  
\_\_\_\_\_ number of days
2. When you experienced pain, can you tell me how severe the pain was on a scale from 1-10, 1 being no pain and 10 being terrible pain
3. On average, how long would your pain last?
  - a. Minutes
  - b. Hours
  - c. Days
  - d. The entire time, I am still in pain
4. Since your last treatment have you experienced any of the following symptoms?:
  - Swelling, redness, or sore skin in and around the treatment area yes/no  
If yes, did you see a doctor for these symptoms y/n  
If yes, please describe the instructions and treatments that the doctor provided
  - Pus or blood (drainage of pus or blood) in or around the treatment area yes/no  
If yes, did you see a doctor for these symptoms y/n  
If yes, please describe the instructions and treatments that the doctor provided
  - A bad odor coming from the treatment area yes/no  
If yes, did you see a doctor for these symptoms y/n  
If yes, please describe the instructions and treatments that the doctor provided
  - Holes or openings in or around the treatment area yes/no  
If yes, did you see a doctor for these symptoms y/n  
If yes, please describe the instructions and treatments that the doctor provided
5. Since your last treatment did you use nair or shaving for your pilonidal disease?
  - Yes, I used nair only
  - Yes, I used shaving only
  - Yes, I used both nair and shaving
  - No, I did not use either
6. Since your last treatment how often have you used nair (branch from 1 or 3)?
  - More than 1 time per week
  - 1 time per week
  - At least 2 times since the last treatment
  - At least 1 time since the last treatment
  - I did not use the nair at all since my last treatment
7. Did someone help you with applying the nair to the treatment area?
  - Yes
  - No
8. Since your last treatment how often have you shaved (branch from 2 or 3)?

PROTOCOL TITLE: A randomized controlled trial of laser hair depilation in adolescents with pilonidal disease

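### Adverse outcomes and treatment-related pain are to be compared between arms, but treatment harm is defined and actively sought only for laser, so the comparison is not like with like

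*Combined protocol and SAP*

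**What the plan says.** The Study Summary and section 2.1 set the comparison: "The secondary objective is to compare adverse outcomes, treatment-related pain, length of stay, disability days, costs and burden of care", followed by other outcomes, for laser plus depilation against depilation alone. Section 17.1 gives no separate safety analysis. It says "Other outcomes will be compared using chi square tests, if categorical", with t or Mann-Whitney tests for continuous outcomes.

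Section 4.2 names one study-specific harm: "study related SAE (second degree burn or pain score >8"). It presents this as tolerance of laser treatment, and the first column of Table 3 is headed "Number of laser treatment patients". Section 6.4 asks for a pain score immediately and 24 hours after treatment, under a heading restricted to the intervention group. Section 6.3 says "An attending surgeon will assess each patient before and after each treatment". At months 1 to 4, laser patients complete surveys in person. Controls do so by phone, email or web unless they book an optional visit.

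On cream, section 3.2 accepts that "there can be some local skin irritation on the site of application". Section 6.2 has both arms using cream or razor at home. Section 15.1 lists only loss of confidentiality as a risk for the chemical/mechanical group. The sample questionnaire in the Appendix asks about "Swelling, redness, or sore skin in and around the treatment area yes/no", and about pus or blood, odour and openings.

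**The concern.** A between-arm comparison of harm is interpretable only if the same events are defined in both arms and looked for equally hard. Here the one defined harm can arise only in the laser arm, and the closest observation happens there too. Skin injury from cream or razor could occur in either arm, but a laser patient is seen by a surgeon at every session, while a control may never be examined after the initial visit.

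Two things are at stake. Laser could appear less safe when total skin injury is equal. And if laser reduces the need for cream and shaving, any resulting fall in their injuries would go largely unmeasured. The objective affected is secondary; the primary recurrence endpoint is a separate matter.

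**Working it through.** The plan gives no harm rate or detection rate, so there is no figure of its own to reproduce. The check sets the provisions side by side and then shows how unequal detection would behave under stated assumptions.

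**Ascertainment by arm**

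| Element | Laser arm | Control arm | Source |
|---|---|---|---|
| Defined treatment harm | Burn or severe pain | None | 4.2, Table 3 |
| Pain immediately and at 24 h | After each session | Not collected | 6.4 |
| Surgeon assessment in the treatment phase | 5 sessions × 2 = 10 | None scheduled after the initial visit | 6.2, 6.3 |
| Month 1-4 surveys | In person | Phone, email or web; visit optional | 6.4 |
| Cream or razor use | Yes | Yes | 6.2 |
| Definition of cream or razor injury | None | None | none shown |
| General adverse-event review and grading | Yes | Yes | 4.2 |

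Five sessions have four gaps of 4 to 6 weeks, so the treatment phase lasts 16 to 24 weeks.

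**What the questionnaire can identify.** The symptom items ask whether a sign was present, whether a doctor was seen and what was done. They do not ask the cause, and redness, soreness, pus and blood overlap with pilonidal disease. One item does name shaving and cream, but its stem asks about trouble that the disease caused. The pain-days item also concerns pain from the disease. No item shown measures pain caused by hair removal in controls, although treatment-related pain is a stated between-arm comparison.

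**Illustration.** Let p be the true proportion harmed, equal in both arms, and s the proportion of that harm detected.

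Observed difference (laser minus control) = p × (s_laser − s_control)

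Neither p nor s is in the documents. Taking s_laser = 0.90, in percentage points:

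| s_control | p = 5% | p = 10% | p = 20% |
|---|---|---|---|
| 0 | 4.5 | 9.0 | 18.0 |
| 0.25 | 3.25 | 6.5 | 13.0 |
| 0.50 | 2.0 | 4.0 | 8.0 |
| 0.75 | 0.75 | 1.5 | 3.0 |
| 0.90 | 0 | 0 | 0 |

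For example, 0.10 × (0.90 − 0.50) = 0.040.

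With the plan's 122 evaluable patients per arm and a two-sided 5% normal-approximation test, the chance of a nominally significant false excess at p = 10% is about 59%, 23% and 6% for control detection of 0.25, 0.50 and 0.75. The artefact matters if control detection is poor and fades as detection evens out. The documents do not show where this trial lies.

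**Internal differences in section 4.2.** Severe pain is a score above 8 in one paragraph and 8 or above in others, so a score of exactly 8 counts under one reading only. Burns are second degree in some places and deep second degree in another.

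**The case against.** The strongest reply is that control harm is not invisible. The questionnaire asks about skin symptoms whether or not a doctor was seen, and its wording is adapted to the time point. Section 4.2 requires quarterly review of all adverse events in the trial and grades them all for relatedness. Section 6.3 provides a 24-hour pager, and controls have monthly contact and optional visits. This stands. A reader might infer that control harm is near zero by construction, or that no survey item touches it. The documents support neither. Only the count of the laser-defined event is structurally zero in controls.

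The burn-or-pain composite is a stopping criterion, and neither section 4.1 nor Table 2 lists it as a between-arm outcome. This also stands: nothing says it will be tested against controls. But the stated objective includes adverse outcomes and treatment-related pain, and no listed outcome gives a common measure of treatment harm. The listed complications are disease-related or post-operative.

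Cream and razor injury is undefined in both arms, and home injuries may heal between laser visits. That limits detection in the laser arm as well, but it does not equalise the two arms.

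The visit schedule was a reasoned choice, explained in section 6.2, and monthly clinic visits for controls are not needed to meet the point. Finally, the questionnaire is labelled a sample and the full forms are attachments not shown, so a dedicated item elsewhere cannot be excluded.

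**Conclusion.** The point holds as one of differential ascertainment in a secondary objective. Treatment harm is defined and actively solicited only for laser. Injury from cream or razor has no event definition, and no item shown attributes it. General adverse-event rules govern events once they surface but do not make them equally likely to surface. The likely direction is against laser. The size is unknown: the differences in the table rest wholly on assumed harm and detection rates and should not be read as estimates. The conclusion also assumes that the unseen survey forms contain no hair-removal-injury item. It does not touch the primary endpoint or the laser stopping rule. The change is worth making because it is cheap and the objective is stated.

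**What to change.** 1. Add one identical item to both arms' surveys at 1, 2, 3, 4, 6, 9 and 12 months. It should ask about any burn, blister, cut, rash or pain caused by hair removal (laser, cream or razor) and whether medical care was needed. Use the same recall wording, since the last survey, in both arms.
2. In section 17.1, base the between-arm comparison of adverse outcomes and treatment-related pain on this item plus record-confirmed visits.
3. Report session burns and 24-hour pain as a laser-only rate with an exact interval and no between-arm test. Section 4.2 already estimates a laser-only percentage with confidence limits, so this needs no new data, covers patients already enrolled and leaves the Table 3 rule as it is.
4. Reconcile the two pain thresholds and the two burn descriptions in section 4.2.

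The cost is one REDCap item and a short addition to 17.1. There are two downsides. Patients already enrolled will lack early responses, so the comparison will use fewer patients. And patients who know their treatment will be attributing cause themselves, so some reporting bias will remain; the record-confirmed visits are a partial check on it.
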